### Secondary outcomes and process measures

The secondary outcomes include both effectiveness and process measures. The trial is not powered to detect significant differences in effectiveness outcomes. A mix of quantitative and qualitative measures will be used to undertake a process evaluation and to inform sample size estimates for a future trial.

#### Secondary outcomes (effectiveness)

The secondary outcomes will be:
Change in salt content of food purchases in the shopping basket, measured as salt in grams per 100 g (and in grams per megajoule) in the intervention compared to the control group; assessed throughout the study through collection of the nutrient composition of all purchased products.Change in salt intake measured through urinary sodium analysis in the intervention compared to the control group; assessed using 24-h urine collection during the baseline period and at the end of the 6-week follow-up appointment. Sodium excretion, reported as millimoles per litre, millimoles per 24 h and total volume of the urine sample, will be converted to daily salt intake in grams using the equation: 17.1 mmol of sodium = 1 g salt, and assumes all of the sodium was derived from salt.Change in blood pressure (systolic and diastolic) in the intervention compared to the control group; recorded at baseline and at the 6-week follow-up.

#### Process measures

The process measures will be:
Recruitment rates: total recruited and number per practice per month, (including the number invited who were eligible and consented, and the number of recruited participants that completed all baseline assessments and were randomised).Acceptability of the intervention delivery. The perspective of the healthcare professionals responsible for delivering the intervention will be captured via interviews, exploring barriers to and facilitators of delivery and their confidence and belief in their capability to deliver the intervention session.App use and acceptability; measured quantitatively through within-app automatic recording (e.g. frequency of use, number of products scanned per user, frequency of swaps presented and accepted, use of specific behaviour change functionality such as goal setting), and measured qualitatively through the post-intervention survey and think-aloud accompanied shopping trips.Feasibility of data collection: willingness of participants to submit 24-hour urine samples and completeness of shopping data (including completeness of data on the salt content of purchased foods).Evidence of contamination; measured as use of the Salt Swap app by the control group.Changes in participant knowledge, perceptions and behaviours in relation to salt intake and health, measured qualitatively through participant questionnaires and semi-structured interviews.

### Sample size

This study is a feasibility study and is not powered to detect a significant intervention effect. However, we calculated that a sample size of 40 was sufficient to estimate our progression criteria outcomes within acceptably narrow confidence intervals to enable robust testing of the trial methods. Recruiting 40 patients will enable the anticipated follow-up rate of 80% to be estimated within +/− 12% (80%, 95% C.I. 68–92).

### Planned analysis

Baseline characteristics will be reported by trial arm using summary descriptive statistics.

#### Progression criteria

Descriptive statistics with 95% confidence intervals will be reported. Progression criteria will use data from all randomised participants.

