## Methods

### Trial design and setting

This trial will be an individually randomised, parallel, two-arm, controlled feasibility trial with a 2:1 (intervention to control) allocation ratio. The primary outcome will be the criteria to progress to a full trial. Process evaluation and analysis of effectiveness outcomes may inform a future trial. Participants will be recruited through five primary care practices in Oxfordshire, UK.

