### Recruitment

Practices will search the electronic health records of registered patients to find people who meet the age and blood pressure inclusion criteria. Prior to sending out the invitation letters, the general practitioner (GP) will screen the search results to ensure that all those identified are medically appropriate to participate in the trial and meet the clinical inclusion criteria. The practice will send potential participants an invitation letter asking them to contact the research team if they are interested in participating; the letter will also include a link to an electronic version of the participant information sheet. GPs may also identify eligible patients opportunistically during routine consultations or via the National Health Service (NHS) Health Check programme. We will aim to randomise 40 participants in the study.

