### Randomisation

Once participants have provided consent and completed the baseline data collection, the research team will randomise them to one of the two trial arms using computer-generated randomisation. The randomisation will be stratified by general practice using block randomisation in blocks of six. A researcher not involved in taking consent or measuring study outcomes will generate the random number sequence using an online random sequence generator (www.sealedenvelope.com) and assign participants to the intervention groups according to the allocation sequence, to ensure allocation is concealed from the rest of the research team until interventions are assigned. Both the research team and participants will be unaware of the treatment allocation prior to consent.

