### Primary outcomes

The primary objective of the trial is to determine whether to progress to a full trial or whether substantial amendments to the trial procedures are required. Based on previous trials of a similar nature we would hope to achieve 80% for the first two progression criteria. Allowing for the 95% confidence interval around this point estimate, we have set the minimum criteria for immediate progression at 65%.

Level one: the following criteria must be met to progress to a full trial with minimal amendments to trial procedures:
That 65% of participants attend the follow-up session.Healthcare professionals typically conduct a brief advice session where at least four out of six of the essential intervention elements are present, assessed by comparing the delivered intervention against a checklist of the components required by the protocol, using audio recordings of the consultation.At least 50% of participants use the app to scan products on at least one occasion by the end of month one.

Level two: the following criteria must be met to continue to a full trial with substantial amendments to trial procedures:
At least 40% of participants attend the follow-up session.Healthcare professionals typically conduct a brief advice session where at least a mean of three out of six of the essential elements are present.At least 40% of participants use the app to scan products on at least one occasion by the end of month one.

If level-two criteria are not met, it would not be considered feasible to continue to a full trial with this trial design.

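### Read literally, the app-use progression criterion divides by all 40 randomised participants although only the intervention arm is offered the app, which raises the 50% mark to about 74%

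*Protocol article*

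**What the plan says.** The Progression criteria paragraph of the Planned analysis gives one data set for all three criteria: "Progression criteria will use data from all randomised participants". It makes no exception for any of them.

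Under Primary outcomes, the level-one app criterion is "At least 50% of participants use the app to scan products on at least one occasion by the end of month one". The level-two version is "At least 40% of participants use the app to scan products on at least one occasion by the end of month one". Neither names an arm. The consequence of falling short of level two is explicit: "If level-two criteria are not met, it would not be considered feasible to continue to a full trial with this trial design".

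The Objectives identify the app as Salt Swap. It is therefore not ShopScanner, the recording app that the Baseline section gives to everyone. The Intervention section introduces Salt Swap during the advice session. The Control (usual care) section gives controls a posted booklet and no app. The list of process measures includes "Evidence of contamination; measured as use of the Salt Swap app by the control group".

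**The concern.** The named data set does not fit this criterion. About a third of the randomised participants are not meant to have the app, so placing them in the denominator caps the achievable rate well below 100% and raises the real pass mark for those who are offered it. It also lets one event count in two opposite ways: a control who scans a product would help the trial to pass, and would at the same time be evidence of contamination.

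The progression criteria are the primary outcome of this study. App use is one of three criteria that decide between progressing with minimal amendments, progressing with substantial amendments, and judging the design not feasible. If the denominator is open to two readings, the same data can lead to different decisions, and the choice could be made after the data are seen.

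**Working it through.** **Inputs.**
- Total randomised: 40 (Recruitment: "We will aim to randomise 40 participants in the study").
- Allocation: 2:1 (Trial design and setting: "controlled feasibility trial with a 2:1 (intervention to control) allocation ratio"). 40 × 2/3 = 26.7, taken as 27 intervention and 13 control.
- Pass marks: 50% (level one) and 40% (level two), from Primary outcomes.
- Assumption: no control uses Salt Swap.

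**The plan's own figure.** The Sample size section gives ±12 points for an 80% follow-up rate with n = 40. The Wald half-width is 1.96 × √(0.8 × 0.2 / 40) = 0.124, or 67.6% to 92.4%. The figure reproduces, but it is for follow-up attendance only. The section gives no figure for app use.

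**Users needed under each denominator.**

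| | All 40 | Intervention arm, 27 |
|---|---|---|
| Level one | 0.50 × 40 = 20, i.e. 20/27 = 74.1% of those offered the app | 14 (14/27 = 51.9%) |
| Level two | 0.40 × 40 = 16, i.e. 16/27 = 59.3% | 11 (11/27 = 40.7%) |
| Highest possible rate | 27/40 = 67.5% | 100% |

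**Where the two readings disagree on this criterion.**

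| Users among the 27 | Intervention-arm denominator | All-40 denominator |
|---|---|---|
| 10 or fewer | below level two | below level two |
| 11–13 | level two | below level two (27.5–32.5%) |
| 14–15 | level one (51.9–55.6%) | below level two (35.0–37.5%) |
| 16–19 | level one | level two (40.0–47.5%) |
| 20 or more | level one | level one |

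**Chance of passing level one.** With X ~ Binomial(27, p), this is P(X ≥ 14) for the intervention-arm denominator and P(X ≥ 20) for all 40.

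| True use p | Intervention arm | All 40 |
|---|---|---|
| 50% | 50.0% | 1.0% |
| 60% | 85.5% | 9.5% |
| 70% | 98.6% | 41.1% |
| 80% | >99.9% | 84.4% |

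**Chance of missing level two at p = 60%.** Intervention arm: 1 − P(X ≥ 11) = 1 − 0.987 = 1.3%. All 40: 1 − P(X ≥ 16) = 1 − 0.613 = 38.7%.

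**Sensitivity to the split.** The design states "The randomisation will be stratified by general practice using block randomisation in blocks of six", so unfilled blocks may move the split away from 27:13. With 26 intervention participants the all-40 marks become 20/26 = 76.9% and 16/26 = 61.5%. With 28 they become 20/28 = 71.4% and 16/28 = 57.1%. At exactly 2:1 they are 75% and 60%. The conclusion does not depend on the exact split.

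**The case against.** The strongest reply is that the sentence has a different purpose. The neighbouring paragraphs limit the effectiveness analysis to people with both measurements, and base the process measures on all available data whether or not people withdrew. In that sequence, the progression sentence may mean only that drop-outs are not removed. The same sentence also covers session fidelity, which is scored from recordings of a session that controls do not have, so it cannot literally mean all 40 for every criterion. The Follow-up section puts the app questions only in the intervention group's questionnaire, and control use already has its own place as contamination. A sensible analyst might therefore use the intervention arm unprompted.

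Much of this stands. The drop-out reading is plausible and may be what the authors intended. What does not follow is that the text is adequate. No sentence in the article limits the app-use denominator to the intervention arm, and the one sentence that names a data set points the other way.

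A reader might go further and infer that the plan is bound to give a wrong decision. The article does not support that. The two readings differ only when 11 to 19 of the 27 use the app, and only if the sentence is applied literally; at 80% true use the literal rule still passes level one 84.4% of the time. A reader might also infer that the protocol regards control use as a failure of the design. It does not: it lists such use as a process measure. Finally, the start of month one and the data set for fidelity could be specified more closely, but an article may leave such detail to the full protocol, and neither is part of this point.

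**Conclusion.** The point holds as a defect in the stated rule. Applied literally, the rule raises the level-one mark from 50% to about 74% of those offered the app, and the level-two mark from 40% to about 59%. With 14 or 15 users of 27, the app criterion moves from the highest category to the lowest on the choice of denominator alone. At 60% true use, the chance of passing level one is about 86% or about 10%.

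These figures assume a split near 27:13, no control use of Salt Swap, and independent use between participants. They describe the app criterion alone; the overall decision also needs the other two criteria. Whether harm would follow depends on how the analyst reads the sentence, which is why it should be settled in the text before the data are seen.

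**What to change.** In the Progression criteria paragraph of the Planned analysis, and in the app criterion at both levels under Primary outcomes, name the denominator:

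- Follow-up attendance: all randomised participants.
- App use: all participants randomised to the intervention arm. Those who do not attend the intervention visit or who drop out stay in the denominator as non-users.
- Control-arm use of Salt Swap: reported only as contamination, and not counted towards the criterion.

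This is a few phrases of wording and needs no new data. The small downside is precision, because the app-use interval then rests on about 27 people. Its half-width is 1.96 × √(0.5 × 0.5 / 27) = 0.189, about ±19 points at 50%, and 1.96 × √(0.8 × 0.2 / 27) = 0.151, about ±15 points at 80%. Both are wider than the ±12 points quoted for follow-up, and the Sample size section could say so.

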#### Effectiveness measures

The analysis will test the change in urinary sodium and change in blood pressure. These effectiveness outcomes will be analysed on an intention-to-treat basis, using regression with baseline adjustment to calculate difference in means, and we will present these summary statistics with 95% confidence intervals. We will test for normality of the residuals and use the non-parametric Mann-Whitney U test, if this model is unacceptable. The analysis will test the change in salt content of food purchases from baseline over the 6-week follow-up, using linear mixed-effects regression models to account for repeat observations. Effectiveness analysis will be based on data from all participants for whom both a baseline and a follow-up measure is available. We will examine the sensitivity of the results to confounding due to differences in baseline characteristics. We will also adjust for the number of people in the household.

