#### Baseline run-in period

The baseline period will run for 2 weeks following the baseline assessment visit. Participants will be asked to collect a 24-hour urine sample within this baseline period, for the measurement of urinary sodium excretion (mmol/24-hour). They will also be asked to submit their grocery shopping till receipts for this period to the research team. Participants who return partial baseline data will be prompted, by phone or email, to return all requested data.

Participants will be randomised once the urine sample and baseline shopping data for the baseline period have been provided. Participants who do not complete these measures will not be randomised. Participants randomised to the intervention group will be booked to attend an intervention session with a HCP at their GP practice. Control participants will receive the control intervention leaflet by post.

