#### Process measures

Descriptive statistics with 95% confidence intervals will be used to report the process measures. Process measures will be based on all data available, regardless of whether participants completed the trial or withdrew. We propose to use framework analysis, a thematic research method, to analyse the data from the think-aloud shopping sessions and retrospective interviews [29, 30].

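### The urinary sodium and blood pressure analyses are labelled intention-to-treat, but the stated analysis set is complete cases by allocated arm

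*Protocol article*

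**What the plan says.** All references are to the protocol article.

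- **Label** (Planned analysis, Effectiveness measures), for urinary sodium and blood pressure: "These effectiveness outcomes will be analysed on an intention-to-treat basis, using regression with baseline adjustment to calculate difference in means".
- **Analysis set** (same paragraph, three sentences later), for the effectiveness analysis as a whole: "Effectiveness analysis will be based on data from all participants for whom both a baseline and a follow-up measure is available".
- **Condition for randomisation** (Baseline run-in period), after naming the urine sample and shopping data: "Participants who do not complete these measures will not be randomised". Blood pressure is measured earlier still, at the baseline visit (Baseline).
- **Sets used elsewhere in Planned analysis.** Under Progression criteria: "Progression criteria will use data from all randomised participants". Under Process measures: "Process measures will be based on all data available, regardless of whether participants completed the trial or withdrew".

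The only sensitivity analysis that Effectiveness measures names concerns imbalance in baseline characteristics.

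**The concern.** An unqualified intention-to-treat label tells the reader that everyone randomised is represented in the comparison. The set defined in the same paragraph leaves out randomised people who have no follow-up measure. The article distinguishes analysis sets in the neighbouring subsections, so the narrower set for effectiveness reads as a stated choice and not as a detail left to another document.

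The exclusion also happens after allocation is known. The Blinding section says participants and the research team cannot be blinded. The arms differ in burden and contact: an advice session and an app in one, a posted leaflet in the other. Loss related to arm or outcome is plausible, although nothing in the article establishes it.

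At stake is how the estimates are carried forward. The Background wants evidence that the intervention can reduce salt intake in the short term before a definitive trial is justified. The abstract ties that trial partly to evidence of behavioural change, and the main Discussion says the data will inform its power calculations. An effect among those retained, read as the effect in all randomised, could mislead those decisions.

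**Working it through.** **Inputs**

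- Randomised: 40 (Recruitment: "We will aim to randomise 40 participants in the study").
- Allocation: 2:1 (Trial design and setting).
- Follow-up attendance: 80% anticipated (Sample size); 65% for level one and 40% for level two (Primary outcomes).

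**1. The plan's own figure.** Half-width of a 95% Wald interval for 80% with n = 40: 1.96 × √(0.8 × 0.2 / 40) = 0.124. This gives 67.6% to 92.4%, which matches the stated 68–92 after rounding.

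**2. Who is excluded.** The rule needs a baseline and a follow-up measure. Urine and shopping baselines are required for randomisation, and blood pressure is taken at the baseline visit. Missing follow-up is therefore the only practical route to exclusion.

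**3. How many.** Excluded = 40 × (1 − f), where f is the attendance rate. With 2:1 allocation kept among those analysed, the standard error (SE) of a difference in means is SD × √(1/n₁ + 1/n₂), before any gain from baseline adjustment.

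| Attendance f | Analysed | Excluded | SE of arm difference |
|---|---|---|---|
| 100% | 40 | 0 | 0.335 SD |
| 80% | 32 | 8 | 0.375 SD |
| 65% | 26 | 14 | 0.416 SD |
| 40% | 16 | 24 | 0.530 SD |

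These counts use visit attendance. They may understate loss for urine: the second sample can be returned up to a week after the visit (Follow-up), and willingness to provide it is itself a process measure. They do not carry over to purchases, which are recorded throughout the study.

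**4. Possible bias (assumptions, not in the documents).**

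- *Loss depends only on arm and baseline.* The planned baseline-adjusted regression, if correctly specified, is unbiased. Bias = 0.
- *Those lost in one arm differ from those retained by d SD, and loss in the other arm is uninformative.* Shift = (1 − f) × d. For d = 0.25 to 0.5 this is 0.05–0.10 SD at 80%, 0.09–0.18 SD at 65% and 0.15–0.30 SD at 40%. Each is smaller than the SE in the same row of the table.
- *Lost intervention participants keep a fraction k of the completers' benefit, loss is equal in both arms, and lost controls resemble retained ones.* Ratio of completer effect to all-randomised effect = 1 / [f + (1 − f)k].

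| k | f = 80% | f = 65% |
|---|---|---|
| 1 | 1.00 | 1.00 |
| 0.5 | 1/0.90 = 1.11 | 1/0.825 = 1.21 |
| 0 | 1/0.80 = 1.25 | 1/0.65 = 1.54 |

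**5. Would a mixed model that keeps all 40 help?** Take baseline and follow-up as joint outcomes, with equal baseline means and a common covariance matrix. With complete baselines and one follow-up, the likelihood factorises into the baseline distribution and follow-up given baseline and arm. People without follow-up contribute only to the first factor, so the treatment estimate equals that of complete-case baseline-adjusted regression. In 5 simulated trials (27:13, about 30% missing follow-up) the two agreed to six decimals each time. Such a model keeps everyone in the data set but leaves the estimate and the missing-at-random assumption unchanged.

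**The case against.** The strongest reply is that this is loose wording with little consequence. Intention-to-treat may have meant only that people are analysed in the arm to which they were allocated, and the actual set is disclosed in the same paragraph. The outcomes are secondary and unpowered, the article states that limitation, and no numeric progression criterion uses an effect size. A missing-data sensitivity analysis is commonly left to an analysis plan that is not shown. Overall follow-up is already a primary outcome in all randomised participants, and completeness of data collection is a process measure.

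Much of this stands. It limits the severity, and the absence of a sensitivity analysis from an article is not a fault in itself. What remains is that the article fixes both a label and a set, and they do not agree. The allocated-arm reading is possible, but the text does not say it.

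Three stronger readings are tempting, and the documents do not support them:

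- *The effect will be overstated by 25% or 54%.* Those figures (k = 0 above) need every lost intervention participant to have had no benefit, with equal loss in both arms and lost controls like retained ones. They are one extreme of a range that starts at zero.
- *Fitting a mixed model to all 40 would give the as-randomised effect.* For urine and blood pressure it returns the planned regression estimate (step 5).
- *The conflict covers every effectiveness outcome.* The label is attached to urinary sodium and blood pressure. Purchases have a separate mixed model for repeated observations and no intention-to-treat claim, and a person who misses the visit may still have purchase data.

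**Conclusion.** The point holds for urinary sodium and blood pressure. The analysis is complete-case by allocated arm, and it excludes only people lost after an unblinded allocation: about 8 of 40 at 80% attendance, 14 at 65% and 24 at 40%. These counts assume that 40 are randomised and that attendance stands in for having a measure; urine may be worse.

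The direction and size of any bias cannot be known from the documents. It is nil if loss depends only on arm and baseline, and under the moderate departures assumed above it is smaller than sampling error. The finding is therefore modest: a label that promises more than the analysis delivers, on secondary outcomes, in estimates with a declared use in planning a definitive trial. It is worth correcting because it is cheap and affects what may be concluded from those estimates.

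**What to change.** 1. In Effectiveness measures, replace the intention-to-treat label for urinary sodium and blood pressure with complete-case, analysed by allocated arm. Keep the planned baseline-adjusted regression as the main analysis.
2. Add one sensitivity analysis for missing follow-up urine and blood pressure that departs from missing at random, for example no change from baseline, or delta-adjusted imputation over a range stated in advance.
3. Report follow-up completeness by arm, separately for urine and blood pressure.
4. For purchases, state that the planned mixed model uses every participant's available weeks, so that the both-measures rule is not read as dropping partial follow-up.

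Settle this before outcome data by arm are seen. The cost is a change of wording, a small amount of extra analysis and a possibly less favourable estimate to report. No new data or participants are needed.
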